## Abstract

**Aims:**

Congenital heart diseases (CHD) are the most common birth defects in humans. Current clinical newborn screening for CHD has limitations. Digital elaboration of cardiac sounds with diagnostic purposes has been explored in the recent past in adults and older children. We propose to develop a dedicated software for automatic dichotomous clinical classification of heart sounds in newborns.

**Methods and results:**

The Digital Diagnosis of cardiac SOUNDs in paediatric patients (DI_SOUND) study is a multicentre study with two sequential phases: (i) derivation/training and (ii) validation. Each newborn will undergo a digital recording of cardiac sounds (stored as wav file using the Littmann Core Stethoscope) and comprehensive echocardiogram. In the development phase, sound tracings will undergo processing to remove background noise. They will be segmented to generate sound samples of homogeneous suitable tuned duration, and filtered records will be normalized for preventing inhomogeneity in the extracted features. Data analysis will be then implemented based on handcrafted feature extraction. A DI_SOUND classifier algorithm will be developed (**Aim** 1). In the validation phase, consecutive newborns will undergo clinical (standard) screening and digital screening using the DI_SOUND algorithm. Comprehensive echocardiogram will serve as the reference to assess diagnostic performance of the DI_SOUND algorithm (Aim 2). A cost-effective analysis will be used to model marginal cost-effectiveness of digital screening using clinical screening as comparison (Aim 3).

**Conclusion:**

The study will prove if development and validation of a digital classifier of neonatal cardiac sounds is feasible and how this will impact clinical outcomes, patient care, hospital admissions, and screening efficiency.

**ClinicalTrials.gov ID:**

NCT07542509

## Introduction

Congenital heart diseases (CHD) are the most common birth defects in humans.^1^ One newborn out of one-hundred is born with congenital heart disease.^1^ Moreover, the spectrum of structural heart disease (SHD) in newborns include CHD and acquired (yet with early onset) anomalies such as ventricular dysfunction due to inborn error of metabolism, neonatal cardiomyopathy, myocarditis, extreme prematurity, toxins, arrhythmias, pulmonary disease, and other systemic conditions.^2,3^ Timely diagnosis of SHD in newborns and children is associated with improved outcomes in the general paediatric population.^4^ As example, ductal-dependent CHD are a rare group of cardiovascular malformation with heterogeneous anatomical features, sharing the inability to sustain either the pulmonary (ductal-dependent pulmonary circulation) or the systemic (ductal-dependent systemic circulation) circulation at the time of ductal closure. Examples of such condition are hypoplastic left heart syndrome, severe coarctation of the aorta, pulmonary atresia with intact ventricular septum, critical neonatal aortic valve stenosis, critical pulmonary valve stenosis, and other rare more complex congenital lesions.^5–9^ In this case, it is imperative to timely establish the correct diagnosis to ensure ductal patency through prostaglandin infusion and refer patient for care to tertiary paediatric cardiovascular centres.

Although some SHDs in newborns may present with evident clinical abnormalities (such as cyanosis, heart failure, or low cardiac output), in many cases early manifestations may be overlooked leading to late diagnosis and serious adverse events including neonatal death, making SHD screening in neonates an established field of intervention in public health strategies.^4^ Current newborn screening for SHD predominantly relies on brachial and lower extremity pulse oximetry screening (POS) and cardiac auscultation.^4,10–12^ Diagnostic performance of such practice is limited (see Online Supplementary Material).^13^ POS is plagued by moderate sensitivity, in particular if performed during the first 24 h of life. Cardiac auscultation is probably even more limited with sensitivity ranging between 75–85%.^14–16^ Summary of selected evidence regarding newborn screening (including large observational studies, multicentre implementations, and systematic reviews) are reported in the Online Supplementary Material. The literature consistently shows that POS has moderate sensitivity with detection rates generally ranging from about 70–80% for critical CHD (see Online Supplementary Material). Clinical examination alone, particularly auscultation, has significantly lower sensitivity because many neonates with CHD initially appear asymptomatic and may not have clearly audible murmurs.

Although prenatal and neonatal screening of CHD has been associated with increased recognition of disease in newborns a significant number of patients is not correctly identified and delayed diagnosis is still present in western and even more so in developing countries.^16^

Digital elaboration of cardiac sounds with diagnostic purposes has been explored in the recent past in adults and older children.^17–29^ At this stage of knowledge, no study prospectively derived and validated a digital classifier for cardiac sounds exclusively in newborns (age less than 30 days). Lv *et al*. validated an artificial intelligence assisted auscultation platform based on convolutional neural network in a mixed cohort of about 1300 children [mean age 2.4 years (standard deviation 3.1, median 0.9, and age range 1 day to 15.9 years)] with a sensitivity, specificity and accuracy of 98% [95% confidence interval (CI): 97–99%], 91% (95% CI: 87–95%), and 97% (95% CI: 96–98%), respectively. The *k* coefficient for comparison to face-to-face human auscultation was found to be 0.87 (95% CI: 0.83–0.91).^30^ A similar study was performed by Yang *et al*. in older children using an existing large database of cardiac sounds (restricting the analysis on specific congenital heart defects) with lower diagnostic performance.^31^ But so far there is no commercially available and validated tool for automatic diagnostic screening for SHD in newborns and no such tool has ever received clearance for clinical use.

We propose to develop a dedicated software for automatic screening of heart sounds (normal vs. abnormal) in newborns to improve neonatal recognition of SHD in this population.

The **D**igital d**I**agnosis of cardiac **SOUND** in paediatric patients (DI_SOUND) study aims to develop and validate a tool with the overall goal of improving neonatal recognition of SHD.

## Study aims

Aim 1: Develop a binary classifier for normal vs. abnormal cardiac sounds in newborns.

Aim 2: Validate the binary classifier in a consecutive, independent cohort of newborns.

Aim 3: Cost-effective analysis of digital vs. standard screening modality for CHD in newborns.

## Methods and study design

This is a multicentre study and it will be conducted in four paediatric cardiology programmes in Italy (IRCCS Azienda Ospedaliero-Universitaria di Bologna, IRCCS Ospedale Pediatrico Bambin Gesù in Roma, Azienda Ospedaliero-Universitaria Policlinico Umberto I in Roma and Ospedale Monaldi in Napoli) along with an Engineering unit (Politecnico di Milano). The study is composed of two sequential phases: a derivation/training phase (binary classification algorithm development, Aim 1) and validation phase (binary classification algorithm validation and cost-effective analysis Aims 2 and 3) (*Graphical abstract*). The study design is based on SPIRIT 2025 Guideline. IRB approval has been obtained by each clinical unit.

### Study population

#### Derivation phase

Study population will include neonates with known cardiovascular status including newborns with and without SHD. Working definition of SHD is any cardiovascular anomaly that will require longitudinal follow-up or intervention based on current practice. This broad definition of SHD parallels the overall goal of this investigation: to develop a screening tool aiming for high sensitivity and flexible performance across the diverse and heterogeneous morphological and functional spectrum of cardiovascular anomalies in newborns.

#### Validation phase

Study population will include newborns without previous cardiovascular examination and unknown cardiovascular status. Pre-test probability for SHD will be defined: high-risk newborn for structural cardiovascular abnormalities vs. neonates at low-risk (general population risk level). High-risk sub-group will include newborns with existing foetal ultrasound suggesting cardiovascular abnormalities and those with clinical indication for paediatric cardiology evaluation (abnormal neonatal screening, signs/symptoms). Low-risk sub-group (approaching patient level prevalence for structural cardiovascular abnormalities) will include consecutive neonates specifically enrolled for such research aim and without any indication for cardiovascular examination.

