### Study procedure

#### Patient enrolment

For the derivation phase newborns without SHD will be enrolled at the time of discharge from Ob/Gyn programme and newborns with SHD will be enrolled at the time of cardiovascular examination. For the validation phase consecutive newborns will be enrolled at the time of discharge from Ob/Gyn unit.

*
Graphical abstract
* summarizes the study pipeline.

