**Figure 1 ztag103-F1:**
[figure not shown]
Diagram of validation phase. Each newborn with blinded cardiovascular status will undergo clinical screening as indicated by current practice and regulations and digital screening using the DI_SOUND algorithm. Gold standard evaluation will be comprehensive echocardiography. Pertinent diagnostics are reported at the bottom.

Cost-effectiveness validation (Aim 3)

Aim 3 will evaluate the potential impact of digital screening on healthcare utilization and costs compared with current standard clinical screening. The target population will consist of newborns at low risk for SHD, with no prior indication for cardiovascular examination, in order to approximate the prevalence of undiagnosed cardiovascular abnormalities in the general newborn population.

For the purpose of this analysis, outcomes will be explicitly defined as follows:

Prevented unnecessary examinations: cases in which (healthy) newborns with a positive result at standard clinical screening but a negative result at digital screening are subsequently confirmed to be free of SHD (i.e. false positives avoided by digital screening).Missed necessary examinations: cases in which newborns (with SHD) with a positive result at standard clinical screening but a negative result at digital screening are subsequently diagnosed with SHD (i.e. false negatives introduced by digital screening).

A decision-analytic modelling framework will be developed to compare digital screening with standard clinical practice. Model inputs will include estimates of SHD prevalence, test performance characteristics (sensitivity and specificity of both screening strategies), and downstream diagnostic pathways. Cost estimates will be derived from national diagnosis-related group reimbursement schedules to reflect healthcare system expenditures associated with confirmatory examinations and missed diagnoses.

To account for parameter uncertainty and variability, a probabilistic sensitivity analysis will be conducted using Monte Carlo simulation. This approach will allow repeated sampling from predefined distributions of key parameters (e.g. prevalence, sensitivity, specificity, and costs) to generate distributions of expected costs and outcomes for each screening strategy. The primary outcome will be the incremental cost-effectiveness of digital screening compared with standard clinical screening, expressed in terms of cost per unnecessary examination avoided and cost per missed SHD case.

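### Risk strata use the comparator's own result, so on the natural reading the low-risk Aim 3 population holds none of the clinical-screen positives that both Aim 3 outcomes require

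*Protocol article*

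**What the plan says.** Four parts of the protocol article bear on this point.

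- **Strata (Study population, Validation phase).** Besides newborns with a suspicious foetal ultrasound, the high-risk sub-group takes in "those with clinical indication for paediatric cardiology evaluation (abnormal neonatal screening, signs/symptoms". The low-risk sub-group consists of "consecutive neonates specifically enrolled for such research aim and without any indication for cardiovascular examination".
- **Comparator (Clinical software validation, Aim 2).** The comparator is the clinical screen required by Italian law: pre- and post-ductal saturation, femoral pulses and auscultation. Enrolment is block-stratified by risk status, and no ratio is given.
- **Timing.** Patient enrolment states: "For the validation phase consecutive newborns will be enrolled at the time of discharge from Ob/Gyn unit". The Discussion describes current screening as done before discharge.
- **Aim 3 (Cost-effectiveness validation).** "The target population will consist of newborns at low risk for SHD, with no prior indication for cardiovascular examination". Unnecessary examinations prevented are cases in which "newborns with a positive result at standard clinical screening but a negative result at digital screening are subsequently confirmed to be free of SHD". Necessary examinations missed are newborns "with a positive result at standard clinical screening but a negative result at digital screening are subsequently diagnosed with SHD". A decision model with Monte Carlo sensitivity analysis takes prevalence and the sensitivity and specificity of both strategies as inputs. The article does not say which cohort supplies the performance inputs.

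**The concern.** The same clinical screen appears to do two jobs: it sorts newborns into risk strata, and it is the comparator against which the digital classifier is judged. A positive screen moves a newborn out of the low-risk group. Both Aim 3 outcomes need a positive screen, and Aim 3 looks only at the low-risk group. The signs and symptoms criterion adds to the overlap, because low saturation, weak pulses or an abnormal auscultation are themselves components of the screen in Table 2.

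Two things are at stake. Aim 3 would have no observed events of either kind in its own target population. That population would also fail its stated purpose of approximating general newborn prevalence, because the cases that the clinical screen catches would already have been taken out.

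**Working it through.** **Reading the definitions together.**
1. Abnormal clinical screen → high-risk (Study population).
2. Low-risk → no indication for a cardiac examination, hence no abnormal screen (Study population).
3. Aim 3 population = low-risk (Cost-effectiveness validation).
4. Each Aim 3 outcome = clinical positive and digital negative, split by disease status (same section).

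Steps 1–3 leave no clinical positives, so step 4 counts zero of each. No section describes a second screen that sets the stratum separately from the comparator.

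**Inputs for the size.** Validation cohort about 1,900 and prevalence 1% (Statistic plan). Clinical sensitivity (Se) 70–80% and specificity (Sp) 95–99% (Limitation). The article gives no figure for the Aim 3 counts, so there is none to reproduce. The starting point is 1,900 × 0.01 = 19 newborns with structural heart disease (SHD) and 1,881 without.

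**Who leaves the low-risk group.**
- True positives: 19 × 0.70 = 13.3 to 19 × 0.80 = 15.2.
- False positives: 1,881 × 0.01 = 18.8 to 1,881 × 0.05 = 94.1.
- All screen positives: 13.3 + 18.8 = 32.1 to 15.2 + 94.1 = 109.3.

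**What remains.**

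| Se | Sp | Newborns left | SHD left | Prevalence |
|---|---|---|---|---|
| 70% | 95% | 1,792.6 | 5.7 | 0.32% |
| 70% | 99% | 1,867.9 | 5.7 | 0.31% |
| 80% | 95% | 1,790.7 | 3.8 | 0.21% |
| 80% | 99% | 1,866.0 | 3.8 | 0.20% |

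Prevalence is 0.01(1 − Se) / [0.01(1 − Se) + 0.99 Sp]. Within this group every newborn is screen-negative, so clinical sensitivity is 0% and specificity 100% by definition.

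**If screen positives are kept.** Take digital specificity 90% and digital sensitivity 90% (Aim 2 target) to 95% (Aim 1 target), and assume the two screens are independent given disease status.
- Prevented: 18.8 × 0.90 = 16.9 to 94.1 × 0.90 = 84.6.
- Missed: 13.3 × 0.05 = 0.67 to 15.2 × 0.10 = 1.52.

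**Pooled Aim 2 accuracy.** Suppose strata are set by the screen alone, with shares w_H and w_L. Let a be the share of SHD in the high-risk stratum and b in the low-risk stratum. Pooled clinical sensitivity is w_H·a / (w_H·a + w_L·b). At natural shares (Se 70%) this is 13.3 / (13.3 + 5.7) = 70%, as it should be. If w_H is raised above its natural share and the data are not reweighted, sensitivity rises and specificity falls.

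**The case against.** **Timing could be read the other way.** The Aim 2 procedure lists clinical screening after consent, the strata are described in terms of pre-test probability, and Aim 3 speaks of "newborns at low risk for SHD, with no prior indication for cardiovascular examination". If the stratum were fixed before the comparator screen, low-risk newborns could still test positive. This stands as a possibility, so a reader should not infer that zero counts are proven. But the article does not say so. It names an abnormal screen as a stratum criterion, and enrolment at discharge after a pre-discharge screen points against it. The full protocol in the supplement, not shown here, may settle the timing.

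**Aim 3 is a model, not a tally.** A reader might infer that Aim 3 cannot be answered at all. That goes too far: with performance inputs from the whole cohort or from other evidence, the model can give non-zero outputs. The source is not stated, and inputs taken from the low-risk stratum would be degenerate.

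**Aim 2 need not be biased.** A reader might infer that every digital-versus-clinical difference is an artefact of enrolment. The article does not support this. Enrolment is described as consecutive, and at natural shares the pooled accuracy figures are ordinary estimates. Distortion needs both an unnatural block ratio and no reweighting.

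**The size has limits.** The 3.8–5.7 cases left should not be set against the plan's 19–20 as a shortfall, because that target is for the whole validation cohort. The 70–80% sensitivity is given in the Introduction for pulse oximetry in critical disease, whereas SHD here is broader. If true sensitivity is lower, prevalence falls less. Removing foetal-ultrasound positives, which is ignored above, would probably lower it further.

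**Conclusion.** The stratum definition and the Aim 3 outcome definitions conflict and must be reconciled. On the natural reading of the article:

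- the observed count of both Aim 3 outcomes in the low-risk stratum is zero, against roughly 17–85 prevented and 0.7–1.5 missed examinations if screen positives were kept;
- clinical sensitivity and specificity within that stratum are 0% and 100% and carry no information;
- SHD prevalence there is about 0.2–0.3% and not 1%, so the stratum does not stand in for the general newborn population.

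This rests on the screen that assigns the stratum being the same as the comparator screen, with its result known at enrolment. The numbers also assume an unselected cohort of 1,900 and the article's own accuracy ranges. The kept-positive counts assume conditional independence as well. Whether the Aim 3 model and the pooled Aim 2 comparison are affected depends on two things the article leaves open: where the model's inputs come from, and the high-to-low block ratio.

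**What to change.** - Define the risk stratum only from information that exists before the mandated clinical screen and is not part of it, for example the foetal ultrasound. Remove the abnormal-screen criterion and any signs that are components of that screen. Deleting the first alone would leave the overlap through signs and symptoms.
- Run Aim 3 on all consecutive newborns whatever their clinical-screen result, or on both strata reweighted to their population shares.
- Take the Aim 3 performance inputs from that same unselected or reweighted cohort. If block sampling is used, compute pooled Aim 2 accuracy from it too, with the block ratio and population shares stated.

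The cost is an amendment to the stratum definition and the Aim 3 population, best made before validation enrolment starts. It needs no extra patients or procedures. The high-risk stratum becomes smaller, and reweighting, if used, widens intervals slightly. With only about one missed examination expected, the cost per missed case will remain imprecise even after the change.

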
#### Validation phase

Clinical software validation (Aim 2)

After screening of eligible patients written informed consent will be obtained from parents or caregivers.

Clinical screening will be performed as mandated by the Italian law. Pre-ductal (right arm) oxygen saturation and post-ductal (leg) oxygen saturation will be recorded. Physical examination will include femoral arterial pulse detection and face-to-face heart auscultation.

Clinical screening output threshold criteria is summarized in *Table 2*.

**Table 2 ztag103-T2:** Clinical screening output threshold criteria

	Positive screening	Negative screening
**Oxygen saturation**	<95% and/or arm-to-leg difference >5%	>95% and arm to leg difference < 5%
**Femoral arterial pulse**	Absent or reduced	Normal
**Heart auscultation**	Any divergence from normal cardiac auscultation	Normal I/II heart sound, venous hum, physiologic murmur

For this phase we will enrol patients using a block stratification for high SHD risk vs. low (standard) SHD risk status for each newborn.

Heart recordings will be acquired (15 s length) before comprehensive echocardiography by a trained research investigator. Age at recording and echocardiographic evaluation will be planned not before 7 days of post-natal life to allow completion of proper cardio-circulatory transition in the healthy newborns (i.e. ductal closure, pulmonary vascular remodelling, foramen ovale physiologic shunt).

The echocardiography will be performed according to current guidelines by expert paediatric cardiovascular imager blinded to clinical and digital screening results. Preliminary inter- and intra-observer variability between dedicated expert cardiovascular imagers among centres will be performed in small patient subset.

Pertinent anonymized demographics, cardiovascular status, and pertinent research variables will be stored in an encrypted, web-based, research-focused online software.

Digitally anonymized echocardiographic clips will be transferred to the Echocardiography Study Core Lab who will perform the final, formal reading of the exams dichotomizing patient population into normal and abnormal examination. Any potential conflict of interpretation will be solved with consensus and among all Units cardiac imagers.

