## Limitation

The most notable limitation is the absence of reliable data to calculate power for the development/training phase. Second, some severe SHD (among others transposition of the great arteries with intact ventricular septum) may have minimal acoustic correlates, and, therefore, our approach may be of limited efficiency for these lesions. Third, clinical screening modality integrates a variety of non-acoustic information, such as general newborn appearance, breathing pattern, femoral pulses, oxygen saturation. It is possible that clinical screening method may outperform digital screening for specific subsets of congenital lesions. Fourth, the frequency response of the digital stethoscope may change significantly between stethoscope models, and this may affect the ability of the classifier to transfer performance to a different model. To mitigate this aspect, we have decided to disable all digital filtering and equalization upon sound acquisition. Development and validation of diagnostic tool in a specific world region may constitute *per se* a limit affecting world-wide generalizability. Lastly, small/premature neonates (<1.5 kg) were not included in the target population of our study by design. This neonatal population routinely undergoes comprehensive cardiovascular evaluation, including echocardiographic screening, which reduces the potential added value of a digital heart sound–based screening tool in this subgroup. They frequently present with clinical and physiological conditions (such as mechanical ventilation, underlying lung disease, haemodynamically significant patent ductus arteriosus, and pulmonary vascular abnormalities) that may introduce substantial acoustic variability and confound heart sound recordings. These factors would limit both the reliability of data acquisition and the generalizability of a classifier intended for the broader neonatal population. Fifth, we are aware that a specificity of 90% may be considered lower than expected for a screening test, however, few consideration should be made to this regard: (i) specificity for current clinical screening modality is reported to be between 95% and 99% with a much lower sensitivity (70–80%) and (ii) our boundary condition is assumed under worst case scenario but we aim for a significantly higher specificity and in the Supplementary material online, *Table S3* of the Online Supplementary Material we are reporting a summary table for diagnostic performance of our classifier under different scenarios showing a sustainable workload for lower specificity compared with optimal specificity (about 80 false-positive newborns every/1000). Finally, given the clinical fragility of preterm infants, we carefully considered the ethical implications of additional handling and sensor application and examination, including potential risks of infection and discomfort.

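### The day-7 rule, the no-previous-examination condition and enrolment at discharge do not fit newborns with an abnormal screen or symptoms; if these drop out, the Aim 2 comparison probably favours the classifier

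*Protocol article*

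**What the plan says.** Four statements in the protocol article bear on this.

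- **Timing.** Study procedure, Validation phase: "Age at recording and echocardiographic evaluation will be planned not before 7 days of post-natal life". The reason given is "to allow completion of proper cardio-circulatory transition in the healthy newborns". No exception is stated for risk group or symptoms. The same section places the 15 s recording before the echocardiogram.
- **Population.** Study population, Validation phase: "Study population will include newborns without previous cardiovascular examination and unknown cardiovascular status". The high-risk stratum of this cohort nevertheless includes newborns with a suspicious foetal ultrasound and "those with clinical indication for paediatric cardiology evaluation (abnormal neonatal screening, signs/symptoms").
- **Enrolment.** Patient enrolment: "For the validation phase consecutive newborns will be enrolled at the time of discharge from Ob/Gyn unit". The Discussion puts usual discharge at 48–72 h.
- **Background and limits.** For ductal-dependent disease, the Introduction says that "it is imperative to timely establish the correct diagnosis to ensure ductal patency through prostaglandin infusion". The Limitation section concedes that some severe lesions (it names "transposition of the great arteries with intact ventricular septum) may have minimal acoustic correlates", and adds that clinical screening could do better than digital screening for particular lesions.

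The Statistic plan makes net classification improvement against standard screening the main Aim 2 analysis and plans for 19–20 cases.

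**The concern.** The day-7 rule is justified by what happens in healthy newborns but is written for the whole validation phase, including those referred because something already looks wrong. Newborns who present early and severely are the ones most likely to be examined before day 7 or moved to another unit before discharge. The text does not say how they stay in the cohort.

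If they leave it, the loss is not random. It is triggered by a positive clinical screen or by symptoms, so it is tied to the comparator, and it falls on the severe end of the disease. Some of these lesions may be nearly silent. The cases lost would then be enriched for those that the clinical screen finds and the classifier misses, which are the pairs that count against the classifier. With about 20 cases in the denominator, very few losses are enough to move the result.

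**Working it through.** **Step 1: follow one newborn through the rules.** Take a newborn with an abnormal saturation screen on day 2.

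| Course | Rule it meets | Rule it does not meet |
|---|---|---|
| Echocardiogram on or after day 7 | Timing rule | Sits badly with the Introduction on timely diagnosis |
| Echocardiogram before day 7, recording later | Timing rule for the recording | No previous examination and unknown status; recording before echocardiogram |
| Recording, then echocardiogram, both before day 7 | Recording order | Timing rule |
| Transfer before Ob/Gyn discharge | – | Enrolment point never reached |

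No row meets every statement. A low-risk newborn who develops symptoms between discharge and day 7 faces the first three rows. With discharge at day 2–3, that gap is 7 − 3 = 4 to 7 − 2 = 5 days.

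**Step 2: the plan's case number.** At 1% prevalence, 19/0.01 = 1900 and 20/0.01 = 2000 newborns, as printed. The 19–20 cases themselves do not follow from 90% ± 10%: 1.96² × 0.90 × 0.10 / 0.10² = 34.6, so 35 cases. That is a separate matter. Here 20 is used only as the planned count.

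**Step 3: direction and scale.** Inputs:

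- 20 cases (Statistic plan).
- Digital sensitivity 90%, or 18/20 (the Aim 2 target).
- Clinical sensitivity 75%, or 15/20 (assumed; midpoint of the 70–80% in the Limitation section).
- k lost cases, all clinical-positive. The article gives no k; 1 and 2 are assumptions.

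If the classifier would have missed all k, observed digital = 18/(20 − k) and observed clinical = (15 − k)/(20 − k):

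| k | Digital | Clinical | Difference |
|---|---|---|---|
| 0 | 18/20 = 90.0% | 15/20 = 75.0% | 15.0 points |
| 1 | 18/19 = 94.7% | 14/19 = 73.7% | 21.1 points |
| 2 | 18/18 = 100% | 13/18 = 72.2% | 27.8 points |

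If the classifier would have found all k, the differences are (17 − 14)/19 = 15.8 and (16 − 13)/18 = 16.7 points, while digital sensitivity falls slightly (17/19 = 89.5%; 16/18 = 88.9%). The difference in sensitivity therefore rises either way. Digital sensitivity itself is inflated only if the lost cases are ones the classifier tends to miss.

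**The case against.** **The rule speaks of planned timing.** It does not bar an earlier clinical echocardiogram, clinical screening continues as the law requires, and the Introduction is background rather than a study instruction. This stands. A reader might infer that the protocol orders sick newborns to wait until day 7; the text does not support that. What remains is that a newborn examined early no longer fits the population description or the planned age.

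**Drop-out is inferred.** The listed inclusion and exclusion criteria do not exclude an early echocardiogram, and the full protocol in the supplement, not shown, may contain an exception. This is fair and limits confidence. The article's own statements still conflict, which is more than an omitted detail.

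**The comparison could reverse in sign.** A reader might infer this by applying 90% and 75% only to the retained cases. With three lost of 20, digital would be 0.90 × 17/20 = 76.5% and clinical (0.75 × 17 + 3)/20 = 78.75%. The documents do not support that reading: it implies true digital sensitivity far below the planned 90%, and nothing in the article says three cases would be lost.

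**Ductal-dependent lesions would go unevaluated.** This is also too strong. Those not revealed before day 7 stay in, so under-representation is as far as the text goes.

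**Net classification improvement also depends on non-cases.** Healthy newborns with a positive clinical screen could leave by the same route, which would flatter clinical specificity. At the 95–99% specificity in the Limitation section, losing every such newborn would raise clinical specificity by 1 to 5 points. The loss of one or two cases shifts the sensitivity difference by 6.1 or 12.8 points. For the net index the upward direction is therefore probable, not certain.

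**The limits are disclosed.** The article admits weak acoustic correlates and calls the tool complementary. That disclosure does not say such cases may be missing from the denominator.

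**Conclusion.** The point holds as a conflict between the timing rule, the population description and the enrolment point for newborns with an abnormal screen, symptoms or a foetal finding. If those examined or transferred early drop out, digital sensitivity and net classification improvement are probably biased upward, and early-presenting critical lesions are under-represented.

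The size is unknown. The shift from 15 to about 21 or 28 points rests on three assumptions: 20 cases, sensitivities of 90% and 75% across all of them, and one or two lost cases that are clinical-positive and digital-negative. It would be smaller per lost case if the high-risk stratum brings in more than 20 cases, and smaller if the classifier would have detected some of those lost. Recordings never taken cannot be recovered at analysis, so this should be settled before validation enrolment starts.

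**What to change.** 1. **Reconcile the text.** Bring the Introduction, Study population, Patient enrolment and Study procedure into line on the timing and enrolment of newborns with an abnormal screen, a foetal finding or new symptoms. The sponsor's clinicians decide the clinical timing; none is proposed here.
2. **Define the Aim 2 cohort.** State that an early clinically indicated echocardiogram does not remove a newborn, including one transferred before Ob/Gyn discharge, and that this echocardiogram counts as the reference. Apply the rule to newborns with and without disease.
3. **Recording.** Take the 15 s recording at that contact where feasible, and flag it as outside the age window.
4. **Report bounds.** Give the number of cases diagnosed before day 7 without a recording. Show digital sensitivity and net classification improvement with these cases counted as not detected and as detected, beside the recorded-only analysis. Neither extreme needs to be primary.

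In the k = 2 illustration, the bounds on the sensitivity difference are 18/20 − 15/20 = 15 points and 20/20 − 15/20 = 25 points, against 27.8 points in recorded newborns only. The recorded-only figure lies above even the bound most favourable to the classifier.

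**Cost.** A protocol clarification and one analysis-set rule, with no larger sample size. Identifying newborns transferred before discharge takes some site effort, some recordings will fall outside the standard age window, and reported digital sensitivity may be lower.
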